### Follow-up

After each 4 months follow-up education session by the dental assistants, children and caregivers in the intervention group will meet the research assistants for monitoring of the children’s daily oral self-care performance. The research assistants will note the number of seals placed in each child’s daily record notebook and the number of checks in the weekly checklist. Then, the children will be asked questions regarding their health status in accordance with the overall/oral health-related quality of life questionnaires, and their height and weight will be measured. Only the CD4 counts will be measured once a year.

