### Interventions

Children and caregivers in group A will receive an intervention for 2 years (May 2018–April 2020). The main components of the intervention will comprise oral health education sessions and daily oral self-care. Prior to the intervention, two dental assistants from the National Pediatric Hospital will be appointed to receive a 1-day training course in conducting the oral health education sessions and intervention follow-up. Subsequently, these professionals will disseminate oral health education sessions to the children and caregivers under the supervision of the dentist every 4 months during the 2-year intervention period (in total six sessions for each participant). The initial education session will be provided with the contents presented in Table 1. The dental assistants will also provide the follow-up sessions to the initial session. Each 60-min session, including practice of the oral health procedure, will be attended by groups of 10 child-caregiver pairs. The education session will aim to teach the children and caregivers about correct brushing and the importance of daily oral care. Teaching tools will be developed based on publicly accessible basic oral health education materials which are used in Japan and the USA at school or dental clinics [33, 34].

**Table 1 Tab1:** Contents of oral health education session

Session 1: Knowledge	
1. What is tooth decay?	
2. Causes and prevention of tooth decay	
Session 2: Practice	
1. Brushing	
2. Flossing	
Session 3: Evaluation of oral health status	
1. Check plaque status using tester	
Session 4: Home-based daily oral care	
1. What one needs to do at home for daily care	
2. Follow-up schedule	

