### Data collection

The effects of the intervention will be assessed by comparing key outcome indicators among children in the intervention and the control groups. Comparisons between groups will be performed by measuring the outcome indicators at baseline and endline (see definitions in the participant timeline section) in the intervention and the two control groups. The surveys will be administered to children and caregivers using a structured questionnaire. We will also conduct oral health and nutritional status assessments of the children in all groups and investigate the CD4 counts and registered clinical data of children living with HIV in groups A and B.

Six research assistants will receive a 1-day training session to ensure their understanding of the questionnaires. After the training, they will administer the questionnaires to 10 children as a pre-test. Two dentists and two dental assistants will receive a half-day training session for oral health data collection. After the training, they will collect oral health data from five children for a pre-test. The data collected for pre-test will not be included in the main analysis.

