#### Clinical records

The clinical records of children living with HIV will be collected by research assistants from the registered documents of the National Pediatric Hospital. The following data will be recorded for the study purposes: CD4 count, history of opportunistic infections, ART regimen, and duration of ART use.

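### Quality-of-life questionnaires are repeated between baseline and endline in the intervention group only (about 7 administrations against 2), which may affect the endline quality-of-life comparison

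*Protocol article*

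**What the plan says.** - **Follow-up:** after each 4-monthly session, "children and caregivers in the intervention group will meet the research assistants for monitoring of the children’s daily oral self-care performance". The research assistants first count the seals and checklist marks. Next, "the children will be asked questions regarding their health status in accordance with the overall/oral health-related quality of life questionnaires". Body size (height, weight) is recorded at the same visit. The paragraph ends: "Only the CD4 counts will be measured once a year". That sentence names no group. It marks CD4 as the exception, so the other items are taken at every visit.
- **Interventions:** sessions are held "every 4 months during the 2-year intervention period (in total six sessions for each participant").
- **Data collection:** "Comparisons between groups will be performed by measuring the outcome indicators at baseline and endline", in the intervention group and both control groups. The same section takes CD4 for groups A and B. The Participant timeline section likewise rests efficacy on baseline and endline.
- **Questionnaires:** the child questionnaire, which holds both quality-of-life scales, is for ages 6–15 only.
- **Clinical records:** the records of children living with HIV, CD4 included, "will be collected by research assistants from the registered documents of the National Pediatric Hospital".
- **Randomization:** research assistants and the study team are blinded only until the baseline assessment is complete.
- **Outcome measures:** DMFT is primary and CD4 secondary. Quality of life is among the further outcomes, and the second study objective also names it.

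**The concern.** A between-arm comparison of a self-reported scale assumes that the scale is administered alike in each arm. Here one arm answers it repeatedly, each time after a lesson on oral care and a check of whether the child has done the home routine. The other arms answer it twice, outside any such setting.

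By endline, group A children are practised respondents who are used to reporting on their health within the intervention programme. Children in groups B and C are not. If that changes how they answer, the change appears as a difference between arms. An analysis of baseline and endline values cannot separate it from a real effect on quality of life. Blinding does not help, because none is stated for children or interviewers after baseline.

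What is at stake is the quality-of-life part of the second objective, not the primary result.

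**Working it through.** **1. Number of sessions (the plan's own figure).** Inputs from Interventions: 24 months, one session every 4 months. 24 / 4 = 6, which matches the stated six. One is the initial session, leaving 6 − 1 = 5 follow-up sessions, at months 4, 8, 12, 16 and 20 if the first is at month 0.

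**2. Quality-of-life administrations per child aged 6–15.**
- Group A: baseline (1) + follow-ups (5) + endline (1) = 7.
- Groups B and C: baseline (1) + endline (1) = 2.
- Variant: with sessions at months 4 to 24, group A has 7 if the month-24 visit is also the endline survey, and 8 if the two are separate.

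The contrast is therefore 7 to 8 against 2. This assumes that the age limit in Questionnaires also applies at follow-up visits.

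**3. Children concerned.** Recruitment takes 20 children per year of age. Ages 6–15 are 10 age groups, so 10 × 20 = 200 of the 260 in each group. After the 10% attrition allowed for in Sample size, 200 × 0.9 = 180.

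**4. Sensitivity (illustration only).** Suppose there is no true effect, and the extra administrations alone move group A's endline score by d standard deviations. With n = 180 per arm, the standard error of the standardized difference is √(2/180) = 0.105. A two-sided 5% test then rejects with probability

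1 − Φ(1.96 − d/0.105) + Φ(−1.96 − d/0.105).

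| Assumed shift d (SD) | Chance of a false positive |
|---|---|
| 0 | 5% |
| 0.05 | 7.6% |
| 0.10 | 15.8% |
| 0.20 | 47.5% |

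The values of d are assumptions. Nothing in the documents supports any one of them, and a shift in the other direction could equally hide a real benefit.

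**5. The other follow-up measurements.**
- DMFT is not in the list of follow-up measurements.
- Height and weight are objective readings, and taking them more often does not change the endline value.
- An additional CD4 test does not change the CD4 count.

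Only the quality-of-life scales remain exposed.

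**The case against.** The strongest case against has four parts.

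- **The interim values are monitoring, not evidence of efficacy.** This is correct: the comparison uses baseline and endline in all groups. The point is therefore not that uncontrolled interim data are misused, but that collecting them may change how group A answers at endline.
- **No shift is demonstrated.** This also stands. Nothing says that group A's endline interview follows a lesson, and no section pairs a child with a particular one of the six research assistants. The documents support a possible effect of unknown size and direction, not a demonstrated bias.
- **Quality of life is neither primary nor secondary, and covers ages 6–15 only.** True, and it limits the importance of the point.
- **Fig. 2, the participant timeline, is not reproduced in the text available here.** It might show interim contacts for the control groups. The written sections give none.

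A reader might infer more from the CD4 sentence: that yearly CD4 is taken in group A only, so that CD4 timing differs by arm, or that endline values from records are old and dilute the effect. The documents do not support this. The sentence names no group, Data collection takes CD4 in groups A and B, and Clinical records gives one hospital source for children living with HIV. Yearly testing in a 24-month trial also fits months 0, 12 and 24. Any figure for dilution or drift would rest on assumed test dates. A rule for the date window of a CD4 value is detail that an article may leave to the full protocol or analysis plan.

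**Conclusion.** The concern holds for quality of life only. As written, children aged 6–15 in group A answer the scales about 7 times (8 on one reading) against 2 in groups B and C, and the extra administrations come after a lesson and a compliance check. With self-report and no stated blinding after baseline, this may affect the endline quality-of-life comparison. The conclusion rests on the written schedule, with Fig. 2 unseen. The false-positive figures show only how sensitive the test would be to assumed shifts.

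It would go too far to say that the endline comparison as a whole is biased: DMFT, height, weight and CD4 values are untouched. This is an avoidable difference in measurement that is cheap to remove, not a threat to the primary result. On CD4, only a clarification of wording is needed.

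**What to change.** In Follow-up, remove the overall and oral health-related quality-of-life questionnaires from the group A visits. Keep the seal and checklist counts as monitoring; height and weight need no change on this account. Quality of life is then asked only at the baseline and endline surveys, 2 against 2, in all three groups.

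This reduces fieldwork. What is lost is the quality-of-life trajectory within group A, which has no comparator and which the efficacy comparison does not use. Asking the questionnaires every 4 months in groups B and C as well would also equalize the count. It would add five contacts per child, however, and the interviews would still follow a lesson in one arm only.

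As a minor clarification at no cost, the CD4 sentence in Follow-up should state that the yearly measurement covers groups A and B alike, in line with Data collection and Clinical records.

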### Outcome measures

The primary study outcome will be the change in oral health status, which will be measured according to the children’s individual DMFT. The secondary outcome will be the CD4 count. The other important outcomes include the salivary pH level, number of cariogenic bacteria, debris index score, salivary flow, nutrition status (height and weight), overall or oral health-related quality of life, and frequency of daily oral care. Details are presented in the data collection section and Fig. 2.

**Fig. 2 Fig2:**
[figure not shown]
Participant timeline

### Participant timeline

The efficacy of the intervention will be evaluated by comparing the intervention and control groups using baseline and endline (2 years after implementing the intervention) survey data. The details are described in Fig. 2.

### Sample size

We calculated the sample size for the intervention and control groups as follows. We estimated that the intervention may suppress the increment of DMFT for around 17% based on the results of a previous study conducted in Cambodia among 8000 uninfected school children in five provinces. In that study, increments of DMFT of intervention and control groups were 0.82 and 0.99, respectively, after a 2-year intervention [35]. According to our situation analysis survey, which was conducted at the same study site in February 2017, for children living with HIV aged 8–15, the mean DMFT was 4.34 (standard deviation 3.3). We estimate that the intervention may suppress the increment of DMFT by 0.7 point, which equates to the 17% decrease in the mean DMFT. To detect this difference in our intervention group, at a power of 80% and a 5% significance level, 260 samples will be required for each group with a potential attrition of approximately 10%. In total, 780 pairs will be required for the three groups.

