**Methods:**

A randomized controlled trial will be conducted in Phnom Penh from May 2018 to April 2020. Among 520 dyads of children living with their respective caregivers, half will be randomly allocated to the intervention group and the other half to the control group. Children aged 3–15 years who are currently receiving antiretroviral therapy at the National Pediatric Hospital will be recruited. In addition, 260 HIV-uninfected children (age-matched to the intervention group) will be recruited from the communities. They, together with their caregivers, will comprise the second control group. The main components of the intervention will include oral health education sessions for the children, as well as daily oral self-care under the supervision of their caregivers. The primary study outcome will be the change in oral health status including the number of decayed, missing, or filled permanent teeth, and the secondary outcome will be CD4 count. The effects of the intervention will be assessed by comparing outcome indicators between the children in the intervention and those in the control groups.

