### Study population and selection criteria

The study will comprise three groups: an intervention arm (group A) and two control arms (groups B and C) (see Fig. 1). The targets of groups A and B will be children living with HIV and their caregivers. Randomization will be performed for groups A and B using a 1:1 allocation protocol. The targets of group C will be HIV-uninfected children and their caregivers, comprising children age-matched with those in group A. Children eligible for groups A and B of the trial must meet all of the following inclusion criteria at randomization: (1) age 3–15 years, (2) have a patient ID at the National Pediatric Hospital, and (3) have received ART for at least 3 months. Children eligible for group C must be aged 3–15 years and must not have been diagnosed with HIV infection. For caregivers in all groups, individuals will be eligible if they are aged ≥ 18 years and self-report as the primary caregiver of the respective child.

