### Recruitment

Recruitment will be conducted via a multiple-step process. First, children living with HIV aged 3–15 years will be identified from the patient lists of the National Pediatric Hospital. According to the list, 1113 children are eligible based on the study criteria. Twenty children in each age category from 3 to 15 years old will be randomly selected from each list to yield 260 children each for groups A and B. Second, the same patient lists will be used to identify one district wherein the largest number of children living with HIV reside. The children in group C will be selected from that district, using lists of residents aged 3–15 years that have been compiled by a local non-governmental organization, in collaboration with the local authorities. Twenty children per age category from 3 to 15 years will be randomly selected from those lists to yield 260 children for group C. The children deemed eligible for the intervention will be provided with information about the study, and the research assistants will seek an expression of interest from the caregivers and the children. They will be contacted by the research assistants to arrange a suitable time for the baseline survey. Prior to the survey, the research assistants will obtain their written informed consent.

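### The sample size inputs come from children aged 8–15, but 38% of each group is selected at ages 3–7, so the stated 80% power is not supported for the 3–15 sample

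*Protocol article*

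**What the plan says.** All references are to the protocol article.

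- **Sample size, survey inputs.** The February 2017 survey at the study site reports, "for children living with HIV aged 8–15, the mean DMFT was 4.34 (standard deviation 3.3").
- **Sample size, target.** The external study of uninfected schoolchildren is summarised as "increments of DMFT of intervention and control groups were 0.82 and 0.99, respectively, after a 2-year intervention", a reduction of about 17%. The article then writes: "We estimate that the intervention may suppress the increment of DMFT by 0.7 point, which equates to the 17% decrease in the mean DMFT".
- **Sample size, conclusion.** "at a power of 80% and a 5% significance level, 260 samples will be required for each group with a potential attrition of approximately 10" per cent.
- **Study population and selection criteria.** Children with HIV are eligible if they meet, among other criteria, "1) age 3–15 years, (2) have a patient ID at the National Pediatric Hospital".
- **Recruitment.** The rule that fills the two HIV arms reads: "Twenty children in each age category from 3 to 15 years old will be randomly selected from each list to yield 260 children each".
- **Abstract, Methods.** "The primary study outcome will be the change in oral health status including the number of decayed, missing, or filled permanent teeth".

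The Outcome measures section sets change in DMFT as primary with no age restriction. The Statistical analyses section plans an intention-to-treat analysis and first stratifies the survey data by ages 3–5, 6–11 and 12–15. No section gives a DMFT mean, SD or expected effect for children with HIV aged 3–7, and none adjusts the sizing inputs to the wider age range.

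**The concern.** A sample size describes a trial only if its inputs describe the children who will be analysed. Here the mean and SD come from ages 8–15, while the recruitment rule deliberately fills five further years of age, 3 to 7, with as many children per year as the older ages. Every one of the 260 is then counted as if the 8–15 target and SD applied.

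The mismatch matters most if DMFT counts permanent teeth, as the abstract says. A child enrolled at 3 is 5 at endline and has few or no permanent teeth to score, so neither arm can show much increment. Such children add to the count but may add little to the difference between arms. A reader who takes the 80% at face value would give a null result more weight than the design can bear.

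**Working it through.** **Inputs.** From Sample size: target 0.7, SD 3.3, mean 4.34, power 80%, alpha 5% (sidedness not stated), 260 per group including about 10% attrition, so 260 × 0.9 = 234 evaluable. From Study population: "Randomization will be performed for groups A and B using a 1:1 allocation protocol". From Recruitment: 20 per year of age.

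**1. The plan's own figure.** With n per group = 2(z_α/2 + z_β)² SD²/Δ²:

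- 2 × (1.960 + 0.842)² × 3.3²/0.7² = 349, or 388 after dividing by 0.9. One-sided, it is 275, or 306.
- The exact 17% of 4.34 is 0.738 (0.7 is 16.1%). With 0.738 the result is 315 (350) two-sided and 248 (276) one-sided.

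None of these attrition-inflated figures gives 260. Two-sided power, Φ(Δ/(SD√(2/n)) − 1.96), for 0.7 and 3.3 is:

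- n = 234: SE = 3.3 × √(2/234) = 0.305; 0.7/0.305 = 2.294; Φ(0.334) = 63%.
- n = 260: 68%.

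This shortfall exists before age is considered.

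**2. Age composition.** Ages 3 to 15 are 13 single years, and 13 × 20 = 260. Ages 8–15 give 8 × 20 = 160 (8/13 = 61.5%). Ages 3–7 give 5 × 20 = 100 (38.5%). After 10% attrition, equal across ages, 144 per arm aged 8–15 remain.

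**3. Ages 8–15 alone, the group the inputs describe.** n = 144: SE = 3.3 × √(2/144) = 0.389; 0.7/0.389 = 1.800; Φ(−0.160) = 44%. At 160 per arm it is 47.5%.

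**4. The enrolled mix.** Let the effect at ages 3–7 be a fraction f of 0.7. The article does not give f, so the range is an assumption.

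- Average difference = 0.7 × (8/13 + 5/13 × f).
- SD case (a): 3.3 at all ages.
- SD case (b): half of 3.3 (1.65) at ages 3–7, analysis adjusted for age: √(8/13 × 3.3² + 5/13 × 1.65²) = 2.78.

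| f | average difference | power, SD 3.3 | power, SD 2.78 |
|---|---|---|---|
| 0 | 0.43 | 29% | 39% |
| 0.25 | 0.50 | 37% | 49% |
| 0.5 | 0.57 | 46% | 59% |
| 1 | 0.70 | 63% | 78% |

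All at 234 per arm, two-sided 5%. Among the combinations tried at this size, power reached 80% (81–83%) only when the full 0.7 held at every age, the SD at ages 3–7 was 30% of 3.3 or less, and the analysis adjusted for age.

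**The case against.** The strongest reply has five parts.

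- **The 0.7 is not purely an 8–15 figure.** This is correct. The 17% comes from the external study of uninfected schoolchildren; only the mean it multiplies, and the SD, come from ages 8–15.
- **The direction of the age effect is assumed.** This stands in part. A smaller SD at young ages works the other way: in case (b) there is no loss against 63% once the effect at ages 3–7 reaches about 59% of 0.7. A low DMFT level at young ages also does not by itself fix a low 2-year increment, and children enrolled at 6–7 are 8–9 at endline, so 10 of the 13 enrolled years of age are 8 or over by then.
- **The permanent-teeth argument rests on the abstract.** The Outcome measures and Oral health status sections say only DMFT, and the Background cites a mean of 7.90 at age 6 against 5.50 at age 12. Those figures are hard to read as permanent teeth alone. But if primary teeth were counted, it would still need to be shown that values from ages 8–15 carry over to ages 3–7.
- **Correcting the increment problem removes these numbers.** The 17% is a reduction in a 2-year increment (0.17 of 0.99) but is applied to a cross-sectional mean. Once target and SD are placed on the increment, 4.34 and 3.3 drop out, and the powers above with them. The age question does not: an increment and an SD of change must still represent ages 3–15.
- **The age strata may deal with it.** How they enter the final model can be left to a fuller plan. They do not repair the sizing, and none of them matches 8–15.

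**Conclusion.** The concern holds in a limited form. The mean and SD, and through the mean the 0.7 target, describe ages 8–15. By design 38% of each group is selected from outside that range, and nothing in the article reconciles the two. The 80% power is therefore not supported for the 3–15 sample.

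Two stronger readings are tempting, and the article supports neither.

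- A reader might infer that the 80% is valid for ages 8–15. It is not: on 0.7 and 3.3 power is about 44% at 144 per arm, and about 63% even if all 234 evaluable children carried the 8–15 effect.
- A reader might infer that the age mix costs a definite number of percentage points. It cannot be fixed from the article. The 29–63% and 39–78% ranges rest on assumed effects and SDs at ages 3–7. A loss is likely if only permanent teeth count, but its size is not established.

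The 62% is the share selected; the share analysed equals it only if attrition is similar across ages. The drop from 80% to 63% is a separate arithmetic matter and should not be attributed to age.

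**What to change.** In the sample size section:

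1. State that 4.34 and 3.3 refer to children with HIV aged 8–15 and that the 17% comes from the external schoolchildren study.
2. Recompute and restate power for the enrolled mix of 20 children per year of age from 3 to 15. Use an age-weighted expected difference in the 2-year DMFT increment and an SD of change, with age in the model.
3. State the values assumed for ages 3–7 and show power over a plausible range.
4. Remove the statement that 260 per group gives 80% power for the whole sample.

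The cost is one recalculation and some rewording. No additional children or visits are needed. The downside is a less favourable stated power and openly assumed values for the youngest ages.

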Although Cambodia has successfully reduced the incidence of new HIV infections, the prevalence of HIV in the general population remains high (0.6% in 2014) relative to that of other Asian countries [25]. In Cambodia, an estimated 4200 children aged younger than 15 years are currently living with HIV [26]; 87% of these children received ART in 2016 [27]. Concomitantly, pediatric oral health is a critical issue in Cambodia. According to the WHO, the estimated mean number of decayed, missing, or filled teeth (DMFT) among 12-year-olds in Cambodia was 5.50 between 2010 and 2012, compared to the global and Western Pacific Region averages of 1.67 and 1.39, respectively [28]. A study of 6-year-old children conducted in Pailin, Kampong Thom, and Kratie, Cambodia, reported the estimated mean number of DMFT as 7.90 [29]. In another study of school children conducted in the capital city of Phnom Penh, the reported mean DMFT was 2.33 [30]. Further, a study conducted in Siem Reap found that more than half of all children aged 6–16 years had dental caries in their permanent teeth [31], a condition that has been largely attributed to poor tooth brushing habits [31, 32]. Oral health is therefore an emerging public health issue in Cambodia that must be addressed.

The proposed research aims to adopt continual and affordable approaches, such as daily oral care, with an intention to improve the overall health status of children living with HIV in Cambodia. The specific objectives of the study are as follows:To examine the effectiveness of the daily oral care intervention in improving the oral health status of these children, particularly suppressing the increment in the number of DMFT relative to their HIV-infected and HIV-uninfected peers without interventionTo examine the effectiveness of the daily oral care intervention on overall health status, particularly including immunity level, nutrition status, and quality of life, relative to their HIV-infected and HIV-uninfected peers without intervention.

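### The 17% reduction in the 2-year DMFT increment is applied to the accumulated mean DMFT, so the 0.7 target and the stated 80% power do not follow from the cited evidence

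*Protocol article*

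**What the plan says.** The Sample size section of the protocol article builds the target in three steps.

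- It takes a relative effect of around 17% from an earlier 2-year study in uninfected Cambodian school children, where "increments of DMFT of intervention and control groups were 0.82 and 0.99, respectively, after a 2-year intervention". Here the 17% describes the increment.
- It reports the team's own February 2017 survey: "for children living with HIV aged 8–15, the mean DMFT was 4.34 (standard deviation 3.3"). This is a score accumulated up to one point in time.
- It combines the two: "We estimate that the intervention may suppress the increment of DMFT by 0.7 point, which equates to the 17% decrease in the mean DMFT".

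The size is then set "at a power of 80% and a 5% significance level", with the result that "260 samples will be required for each group with a potential attrition of approximately 10" per cent.

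The first objective, at the end of Background, is stated in increments: "particularly suppressing the increment in the number of DMFT". Outcome measures defines the primary outcome as a change measured by each child's DMFT, and Participant timeline places the comparison at baseline and 2 years.

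**The concern.** A percentage derived from one quantity has been multiplied by another. The 17% is the fraction by which 2 years of new DMFT was reduced. The 4.34 is the DMFT a child has built up by the survey date, over all the years before it. The product is still called a suppression of the increment, so the text gives the same 17% two different bases.

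The SD has the same problem. The 3.3 is the between-child spread of accumulated DMFT at ages 8–15. The trial compares 2-year changes in children aged 3–15. With 20 children per year of age (Recruitment), ages 3–7 supply 5 × 20 = 100 of the 260 per group, or 38%, and they lie outside the range that produced either figure.

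The design effect for the primary outcome is at stake. If the intervention achieves the relative reduction the protocol cites, the absolute difference may be well below 0.7, and a reader who relies on the stated 80% could misread a null result.

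**Working it through.** **Inputs.** From Sample size: increments 0.82 and 0.99, mean 4.34, SD 3.3, target 0.7, 80% power, 5% significance (two-sided assumed, as the protocol does not say), and 260 per group with about 10% attrition. Evaluable per arm: 260 × 0.9 = 234. The 1:1 allocation is from Study population and selection criteria.

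**The plan's own target.**
- Source effect: 0.99 − 0.82 = 0.17, and 0.17 / 0.99 = 17.2%.
- 17% of the accumulated mean: 0.17 × 4.34 = 0.74, stated as 0.7 (0.7 / 4.34 = 16.1%).

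The 0.7 is therefore 17% of the mean, rounded down. The multiplication is sound; the base is not.

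**The plan's own sample size.** n = 2 × (1.960 + 0.842)² × (3.3 / 0.7)² = 349 evaluable per group, or 349 / 0.9 = 388 enrolled. One-sided, the figures are 275 and 306. Neither gives 260. With 234 evaluable per arm, power for 0.7 is 63% at SD 3.3. It reaches 80% only at an SD of about 2.7. This is a separate discrepancy in the same paragraph.

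**How 0.7 compares with the cited study.**
- 0.7 / 0.17 = 4.1 times the cited absolute effect.
- 0.7 / 0.99 = 71% of the cited control increment.
- For 0.7 to be 17% of an increment, controls would have to gain 0.7 / 0.17 = about 4.1 DMFT in 2 years, nearly the whole 4.34 accumulated so far.

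**Applying 17% to an increment.** The document gives no 2-year increment and no SD of change for children with HIV, so both are assumed here over a range. Power = Φ(target / (SD × √(2/234)) − 1.96), with √(2/234) = 0.0925. The opposite tail adds at most 0.2 of a percentage point in this table.

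| Assumed control increment | 17% target | 0.7 / target | Power, SD 1.0 | Power, SD 1.5 | Power, SD 2.0 | Largest SD for 80% |
|---|---|---|---|---|---|---|
| 0.99 (cited) | 0.17 | 4.1 | 45% | 23% | 15% | 0.66 |
| 1.6 | 0.27 | 2.6 | 83% | 49% | 31% | 1.04 |
| 2.0 | 0.34 | 2.1 | 96% | 69% | 45% | 1.31 |
| 2.4 | 0.40 (0.408 unrounded) | 1.7 | 99% | 82% | 58% | 1.54 |

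The last column is target / (2.802 × 0.0925). As an example, for 0.17 at SD 1.0: 0.17 / 0.0925 = 1.84, and Φ(1.84 − 1.96) = 0.45.

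**The case against.** The best defence is that the plan carries over the relative effect, not the absolute one. The 0.99 comes from uninfected school children. The Background says that children with HIV tend to develop more caries, and the survey mean of 4.34 exceeds the 2.33 it quotes for Phnom Penh school children (ages may differ). The increment in this population could well be above 0.99, which brings the proper target closer to 0.7. The SD of change may also be below 3.3, which works in the trial's favour: for a true difference of 0.7, power with 234 per arm rises from 63% at SD 3.3 to 97% at SD 2.0.

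Both arguments stand, and they limit what can be claimed. A reader might infer that the target is inflated fourfold as a matter of fact, that the evidence supports only a quarter of the planned effect, and that the trial will most likely miss it. The documents do not support that. These figures hold only if the cited control increment of 0.99 carries over to children with HIV, and even for 0.17 power is 45% if the SD of change is 1.0.

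A reader might also infer that the plan expects brushing to reverse DMFT already recorded. It does not; it speaks of suppressing the increment.

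Neither argument justifies the change of base. The protocol does not defend 0.7 by a larger increment in children with HIV. It states that 0.7 is 17% of the mean. Nor is this a matter of condensed reporting, since the derivation is printed in full.

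**Conclusion.** The point holds as a wrong base for the effect size. The 17% is a reduction in the 2-year increment, yet the target is 17% of accumulated DMFT, and the SD likewise belongs to the accumulated score. That much can be read directly from the Sample size section and is certain.

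The size of the error is not certain. Over assumed control increments of 0.99 to 2.4, the 0.7 overstates a 17% reduction by about 4.1-fold down to 1.7-fold. It is right only if controls gain about 4.1 DMFT in 2 years. The stated 80% is not supported for a 17% reduction in the increment unless the increment is well above the cited one or the SD of change is small, at most about 0.66 for a difference of 0.17. All power figures assume 234 evaluable per arm, a two-sided 5% test and a simple comparison of mean changes.

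**What to change.** Rewrite the Sample size paragraph in units of the primary outcome: the assumed 2-year increment in the HIV-infected control group, the SD of the 2-year change, and the absolute difference to be detected, each with its source or marked as an assumption. State that 0.7 is about 71% of the cited control increment. Replace the single 80% figure with power at 260 per group over a stated range of increments and SDs.

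If age-level data from the 2017 survey exist, the slope of DMFT on age times 2 years gives a rough increment. It can only be a guide, because the survey is cross-sectional, covers ages 8–15 and yields no SD of change.

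The cost is a short reanalysis, if the data allow it, and new wording. No extra enrolment is needed. The drawback is a less favourable stated power.
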